**Protocol Title: Evaluating Trikafta for the treatment of patients with non-cystic fibrosis bronchiectasis (NCFBE)**

---

EKG, CFTR genotyping, questionnaire, serum pregnancy test for females, sweat chloride test, and spirometry.

On day 1 (when subject returns), the visit will require approximately 6 hours to complete the concomitant medication review, adverse event assessment, interval medical history, physical exam, O2 saturation, safety laboratory assessments (CBC/Diff, RENAL/LFT chemistry panel, and urinalysis), questionnaire, sweat chloride, urine pregnancy test for females, spirometry, cutaneous punch biopsy (3mm), drug dispensing, and drug administration. The cutaneous punch biopsy may occur at any time between the Screening Visit and Day 1 based on dermatology clinic schedule availability.

- 1 Cutaneous 3 mm punch biopsy (performed here (and on day 56 (or up to two weeks later) if necessary to produce additional iPS cells)): In this procedure, a circular blade is rotated from epidermis to subcutaneous fat, yielding a ~ 3 mm cylindrical core of tissue. Extending the skin perpendicular to the incision line allows for facile closure, which can typically be accomplished with a single suture. Pain is well-managed by local subcutaneous anesthetic. A small fibrotic scar can be minimized by linear closure of the biopsy. Significant pain, bleeding, or infection are very rare.

The subject will complete a phone call visit on day 7 (+/-2) that will require approximately 30 minutes to complete concomitant medication review, interval medical history, and adverse event assessment.

On day 14 (+/-2) the subject will return for a visit that will require approximately 4-6 hours to complete concomitant medication review, interval medical history, adverse event assessment, physical exam, drug dispensing and drug return, questionnaire, safety laboratory assessments (CBC/Diff, RENAL/LFT chemistry panel, and urinalysis), sweat chloride test, EKG, O2 saturation and spirometry.

On day 28 (+1/-2) we will conduct interval medical history, adverse event assessment, concomitant medications, physical exam, sweat chloride test, spirometry, O2 saturation, safety laboratory assessments (CBC/Diff, RENAL/LFT chemistry panel, and urinalysis), questionnaire, and drug return. This visit should require 4-6 hours to complete. This visit should occur no later than Day 29 since a 28-day supply of Trikafta™ will be provided.

The 'wash-out' visit will be conducted on day 56 (+/-2) which will require approximately 4-6 hours to complete concomitant medication review, interval medical history, adverse event assessment, physical exam, safety laboratory assessments (CBC/Diff, RENAL/LFT chemistry panel, and urinalysis), questionnaire, sweat chloride, urine pregnancy test for females, cutaneous punch biopsy (3mm) if necessary to obtain additional cells, O2 saturation, and spirometry. The cutaneous punch biopsy may occur within  $\pm$  14 days of the day 56 visit based on dermatology clinic schedule availability. No further data will be collected after all study procedures and measurements are completed.

**Protocol Title: Evaluating Trikafta for the treatment of patients with non-cystic fibrosis bronchiectasis (NCFBE)**

---

Spirometry may be performed either pre- or post-bronchodilator at Screening. At all other visits, spirometry should be performed pre-bronchodilator. However, if patient is unable to withhold bronchodilator use at the Day 1 visit, then the spirometry assessment will be considered 'post-bronchodilator' and attempts should be made to collect spirometry post-bronchodilator at remaining visits.

In order for a spirometry assessment to be considered pre-bronchodilator, subjects should adhere to the following:

- Subjects should refrain from using short-acting bronchodilators (e.g., albuterol) or anticholinergic (e.g., ipratropium bromide [Atrovent®]) for more than 4 hours before the spirometry assessment.
- Subjects should refrain from using long-acting bronchodilator (e.g., salmeterol) for more than 12 hours before the spirometry assessment; and
- Subjects should refrain from using once-daily, long-acting bronchodilator (e.g., tiotropium bromide [Spiriva®]) for more than 24 hours before the spirometry assessment.

Sources of Patient-Derived Material:

- Review of patient medical records and demographic information
- History and physical exam
- Blood and urine for safety studies (<6 tablespoons of blood per visit)
- Sweat chloride results
- Questionnaire data
- Spirometry (FEV1, FVC, and FEF25-75%) calculated per Hankinson equation
- Cutaneous punch biopsy (3 mm)/iPS cell derivation
- O2 saturation
- EKG
- CFTR genotype
- Pregnancy test
- Drug accountability
- Adverse event assessment
- Concomitant medication review

Note: Data collection forms for the study are in preparation.

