### 6. Procedures Involved

#### Human Subjects Involvement

| Procedures             | Screening/
Enrollment
Day -28 to -1 | Baseline
Visit 1, Day 1 | Study Visit 2
(phone call)
Day 7 +/-2
days | Study Visit 3
Day 14 +/- 2
days | Study Visit 4
Day 28 +/-2
days | Final
Study
Visit Day 56
+/-2 days |
|------------------------|-------------------------------------------|----------------------------|-----------------------------------------------------|---------------------------------------|--------------------------------------|---------------------------------------------|
| Informed consent       | X                                         |                            |                                                     |                                       |                                      |                                             |
| Medical history        | X                                         | X                          | X                                                   | X                                     | X                                    | X                                           |
| Physical exam          | X                                         | X                          |                                                     | X                                     | X                                    | X                                           |
| Cutaneous punch biopsy |                                           | X                          |                                                     |                                       |                                      | X c                              |
| CFTR genotype          | X                                         |                            |                                                     |                                       |                                      |                                             |

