### **7. Statistical Analysis Plan**

Goals of the 'main' study are to determine the clinical response to Trikafta™ and whether *in vitro* responsiveness of iPS cell-derived airway monolayers predict Trikafta™ effectiveness. Primary outcomes comprise the ability of iPSC-derived monolayers to predict respiratory benefit from Trikafta™ after 4 weeks of *in vivo* treatment. Primary analysis will include an estimate of clinical response rate of Trikafta™ at week 4 of treatment and a 95% confidence interval using the exact method proposed by Blaker (Blaker, 2000). A responder is defined as any subject with an improvement, from baseline, in  $FEV_1 > 5\%$  predicted.  $FEV_1$  will also be considered continuously. A two-sided 0.05 alpha level paired t-test comparing the baseline and week 4  $FEV_1$  measurements, along with the test and 95% associated confidence interval, will be evaluated.

In this study, if at least 15% of subjects meet the definition of responder, we will view this as initial evidence of a favorable result. Overall response rate will be accompanied by an exact 95% confidence interval. To determine the role of iPS *in-vitro* response to Trikafta™, we will compare the  $\Delta$  Isc (change in Isc) among Trikafta™ responders and Trikafta™ non-responders using an ANCOVA test. Additionally, we will correlate the  $\Delta$  Isc obtained from *in vitro* experiments with the change in FEV1% predicted (post minus pre) using Spearman's rank-order correlation with an associated 95% confidence interval. We will also test whether the iPS response reaches a CFTR functional threshold of 30% wild-type levels (a magnitude of activity in primary airway epithelial cells viewed as potentially relevant to clinical benefit). In a sensitivity analysis, we will replicate the FEV1 analysis with sweat chloride responses and determine the *in vivo* response rate.

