**Protocol Title: Evaluating Trikafta for the treatment of patients with non-cystic fibrosis bronchiectasis (NCFBE)**

subject research, we will evaluate therapeutic response in individual subjects by an interrupted time series (ITS) method. Briefly, in the absence of an independent control group, ITS analysis is a quasi-experimental design in which each subject acts as their own control and is followed serially in time prior to and after an interruption (in this case, the start of treatment). If the treatment has causal impact, the post-intervention time series will have a different level or slope than the pre-intervention series. Time series models also have the power to test and correct for possible cyclical patterns and outliers. Using segmented regression analysis, we will conduct ITS models for each of the subjects enrolled in the trial. A significant change in slope from the pre-treatment period will indicate a significant treatment effect. ITS models will be constructed for each outcome of interest where historical and pre-treatment data are available. The change in slope will also be correlated with the *in-vitro* response using Spearman's rank-order correlation coefficient.

All analyses will be conducted using the intention to treat principal, where all subjects will be included in analysis regardless of how long they took the study medication. Statistical significance will be assessed at the 0.05 level and analyses conducted using SAS v. 9.4 (SAS Institute; Cary, NC).

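### The N-of-1 analysis may mix pre- and post-bronchodilator FEV1 before treatment, which can create a false slope in either direction; matching of Day 1 and Day 28 is intended but has no fallback.

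*Protocol*

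**What the plan says.** Section 6 (Procedures Involved) sets the collection rule: "Spirometry may be performed either pre- or post-bronchodilator at Screening". Then: "At all other visits, spirometry should be performed pre-bronchodilator". A value counts as pre-bronchodilator after a washout of more than 4, 12 or 24 hours, depending on the agent. If a patient cannot withhold on Day 1, that value is labelled post-bronchodilator and "attempts should be made to collect spirometry post-bronchodilator at remaining visits". No agent, dose or timing is given for a post-bronchodilator value.

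The schedule in Section 6 labels the visits: Screening falls between Day -28 and Day -1, and the next column is "Baseline Visit 1, Day 1".

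Section 7 defines the primary responder: "A responder is defined as any subject with an improvement, from baseline", of more than 5% predicted FEV1. It adds a paired t-test of baseline against week 4. Neither sets a condition on bronchodilator state, and all subjects are analysed. For the modified N-of-1 analysis, segmented regression is fitted to each subject where historical and pre-treatment data exist, with this rule: "A significant change in slope from the pre-treatment period will indicate a significant treatment effect". The change in slope is also correlated with the in vitro response.

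**The concern.** The N-of-1 problem needs no departure from the protocol. A post-bronchodilator Screening test followed by a pre-bronchodilator Day 1 test complies fully. Both values fall before treatment, and the difference between them is a bronchodilator effect that the model sees as a decline. A flat course on treatment then looks like a favourable change in slope. The opposite order, with Screening pre and Day 1 post under the exception, gives a false rise and counts against the drug. Either way the distorted slope change goes into the correlation with the iPSC result, where no significance threshold filters it.

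For the primary endpoint the issue is smaller. The text aims at the same state on Day 1 and Day 28, but in soft wording and without saying what happens when matching fails. A post/pre pair would hide a response; a pre/post pair could create one. There is no control arm in which the error would cancel.

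**Working it through.** **1. The protocol's design figures.** Inputs from Section 7, Sample size: 16 subjects, then 29 in total; stopping is considered at 0 of 16; fewer than 2 of 29 means ineffective; response rates 1% and 15%. The chance of passing is the sum over x = 1 to 16 of P(Bin(16,p) = x) × P(Bin(13,p) ≥ 2 − x).
- p = 1%: 2.78% (stated 2.8%). Early termination 0.99^16 = 85.1% (stated 85%).
- p = 15%: 90.04% (as stated).

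**2. False pre-treatment slope.** The bronchodilator effect B is not in the protocol. I assume 4 points of % predicted (range 3 to 6) and a truly flat course.
- Screening post on Day -28, Day 1 pre, no history: slope = −B/29 × 7 = −4/29 × 7 = −0.97 points per week (−0.72 to −1.45 for B = 3 to 6). By Day 28 a flat course lies 4 × 27/29 = 3.7 points above the extrapolated line.
- Screening on Day -14 instead: −4/15 × 7 = −1.87 points per week.
- Screening pre on Day -28, Day 1 post: +0.97 points per week.
- With two assumed historical values on Days -180 and -90, the mean time is −74.25, the deviations are −105.75, −15.75, 46.25 and 75.25, and their sum of squares is 19,232.75.
  - Only Screening post: 4 × 46.25/19,232.75 × 7 = +0.07 points per week.
  - All values before Day 1 post: −4 × 75.25/19,232.75 × 7 = −0.11 points per week.

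Size and sign thus depend on how much history exists and on its state.

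**3. Sensitivity of the primary rule to one mismatched pair.** Assumptions not in the protocol: bronchodilator effect b of 3 to 6 points and SD s of the FEV1 change of 3 to 5 points. With no drug effect, a Day 1 pre / Day 28 post subject exceeds 5 points with probability q = 1 − Φ((5 − b)/s), which runs from 25% (b = 3, s = 3) to 63% (b = 6, s = 3).

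Put one such subject in stage 1 and hold the other 28 at the protocol's 1%. The chance of passing is q × (1 − 0.99^28) + (1 − q) × 2.56%, where 2.56% is the two-stage result with 15 and 13 subjects.
- q = 0.2525: 0.2525 × 24.5% + 0.7475 × 2.56% = 8.1%.
- q = 0.6306: 0.6306 × 24.5% + 0.3694 × 2.56% = 16.4%.

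So 2.8% becomes about 8% to 16%. In the other direction, if 10% to 30% of true responders were masked by post/pre pairs, power at 15% would fall from 90.0% to between 86.5% and 75.5%.

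**The case against.** A reader might infer that the protocol allows different states on Day 1 and Day 28 and then compares them. It does not. Day 1 is the labelled baseline, so the free choice at Screening does not enter the responder rule or the t-test. The sentence about attempts is itself the matching rule, and if it fails the pair is post then pre, which hides a response. A false response needs pre then post, against the instruction that later visits should be pre-bronchodilator; Section 20 sends deviations to the IRB and the monitoring committee. This stands. What remains is that no fallback is stated.

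A reader might also infer that the time-series artefact always favours treatment. It does not: Screening pre with Day 1 post reverses the sign, and flat history shrinks the slope to near zero and can turn it positive. Moreover, a segmented model with four parameters has no residual degrees of freedom on Days -28, 1, 14 and 28, and one if Day 56 is added. A significant result from one mismatched visit is therefore unlikely without history, and Section 7 mentions correction for outliers. This limits the significance rule but not the correlation with the iPSC result, which uses the slope change itself.

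The 8% to 16% figure holds everyone else at the 1% null. With the same assumed SDs, matched pairs alone cross 5 points by chance in 1 − Φ(5/s) = 4.8%, 10.6% and 15.9% of subjects (s = 3, 4, 5), well above 1%. Measurement noise is then the larger threat, and one mismatched pair adds less. That is a separate matter.

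Finally, the handling of deviating values may sit in an analysis plan that is not shown. The collection rule, however, is in the protocol, and a state that was not recorded cannot be recovered later.

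**Conclusion.** The concern holds mainly for the N-of-1 analysis. Following the protocol exactly can produce a mixed-state pre-treatment series and a false slope of either sign. For an assumed 4-point effect it is about 1 point per week when only Screening on Day -28 and Day 1 are available, more if Screening is closer to Day 1, and about 0.1 or less in the two examples with history.

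For the primary endpoint the defect is limited to soft wording with no fallback. The 2-of-29 rule is sensitive to a few mismatched pairs, but their frequency and the size of the bronchodilator effect are not in the protocol. The documents do not support saying that the responder rate will be inflated. This is worth correcting before data collection, at little cost.

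**What to change.** - Record bronchodilator state and time of last use at every spirometry. Section 6 says the data collection forms are still in preparation.
- Do Screening spirometry pre-bronchodilator where possible, under the washout definition used at the other visits. It cannot be guaranteed that Day 1 will match, because that depends on whether the patient manages to withhold.
- Restrict the N-of-1 FEV1 series to values in the same state as Day 1, or include state as a covariate.
- Require the Day 1 and Day 28 tests to be in the same state. If they differ, repeat the test inside the Day 28 (+1/−2) window given in the text of Section 6. Rebooking beyond Day 29 would conflict with the 28-day drug supply stated there.
- Keep all subjects in the primary analysis, as Section 7 requires, and add a sensitivity analysis limited to same-state pairs.

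Cost: one added item on the case report form, an occasional repeat test within the window, and the loss of some non-comparable historical values from the N-of-1 analysis.

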**Subject recruitment plan**

We plan to recruit 30 subjects with NCFBE into the 'main' study. We intend to include ~50% female and ~50% male subjects age ≥ 18. Subjects will be referred from clinicians participating in the trial (Emory University, Atlanta) or from outside institutions.

All individuals who consent to participate will be evaluated by clinicians at Emory Clinic. Travel, meals, accommodations, etc. for study visits will be covered by funds available through the

## **Protocol Title: Evaluating Trikafta for the treatment of patients with non-cystic fibrosis bronchiectasis (NCFBE)**

---

project, and a payment of \$150 per visit (see also below) will be provided as a gift card to reimburse the subject for the time taken to conduct this study.

### **1. Informed Consent Process:**

Informed consent will be obtained by well-trained study coordinators or investigators using an Institutional Review Board approved document. A consent to allow CFTR genotyping and sweat chloride will be offered as part of the 'lead in' study to identify potential study subjects with CFTR mutations or mildly elevated sweat chloride levels. A second consent form will be available for individuals found by the 'lead in' study to have a single disease-causing CFTR mutation and/or sweat chloride 30-60 mEq/L, but without clinical criteria necessary for a diagnosis of cystic fibrosis. Participants will be asked to sign the informed consent documents only after the study has been fully described to the subject and all questions have been answered. Participants will be offered at least 24 hours to review the consent before the research is to begin, although consent may be obtained on the day of screening if preferred by study subjects (e.g., those traveling from significant distance).

NCFBE is not associated with cognitive or other intellectual limitations. No vulnerable adult subjects are intended for enrolment in the trial. If, in the opinion of the study investigator, a prospective participant lacks sufficient understanding and is therefore not able to provide informed consent, that subject will not be enrolled. The ability to obtain consent represents criteria for inclusion in the trial.

### **2. Compensation for time and effort:**

Travel, meals, accommodations, etc. for study visits will be covered by institutional or other funds (participant and caregiver companion). A reimbursement for time taken to complete the study of \$150 per in-person visit and \$30 at the Day 7 telephone call will be provided as a gift card. All payments will be pro-rated. A payment of \$150 will also be provided if an unscheduled visit is needed (for multiple repeat assessments or cutaneous punch biopsy occurring on another day). If the unscheduled visit is needed just for a repeat laboratory sample collection, a payment of \$30 will be provided. A payment of \$150 will be provided for participation in the 'lead in' study.

### **7. Statistical Analysis Plan**

Goals of the 'main' study are to determine the clinical response to Trikafta™ and whether *in vitro* responsiveness of iPS cell-derived airway monolayers predict Trikafta™ effectiveness. Primary outcomes comprise the ability of iPSC-derived monolayers to predict respiratory benefit from Trikafta™ after 4 weeks of *in vivo* treatment. Primary analysis will include an estimate of clinical response rate of Trikafta™ at week 4 of treatment and a 95% confidence interval using the exact method proposed by Blaker (Blaker, 2000). A responder is defined as any subject with an improvement, from baseline, in  $FEV_1 > 5\%$  predicted.  $FEV_1$  will also be considered continuously. A two-sided 0.05 alpha level paired t-test comparing the baseline and week 4  $FEV_1$  measurements, along with the test and 95% associated confidence interval, will be evaluated.

In this study, if at least 15% of subjects meet the definition of responder, we will view this as initial evidence of a favorable result. Overall response rate will be accompanied by an exact 95% confidence interval. To determine the role of iPS *in-vitro* response to Trikafta™, we will compare the  $\Delta$  Isc (change in Isc) among Trikafta™ responders and Trikafta™ non-responders using an ANCOVA test. Additionally, we will correlate the  $\Delta$  Isc obtained from *in vitro* experiments with the change in FEV1% predicted (post minus pre) using Spearman's rank-order correlation with an associated 95% confidence interval. We will also test whether the iPS response reaches a CFTR functional threshold of 30% wild-type levels (a magnitude of activity in primary airway epithelial cells viewed as potentially relevant to clinical benefit). In a sensitivity analysis, we will replicate the FEV1 analysis with sweat chloride responses and determine the *in vivo* response rate.

Secondarily, we will serially evaluate clinical outcomes of interest prior to and after the start of therapy. Change in clinical measurements (in addition to spirometry – sweat chloride, weight/BMI, quality of life) will be monitored. A complementary analysis evaluating the percentage of participants with  $\geq 15$  mmol/L decline in sweat chloride will also be reported. With a previously estimated 9.7 mmol/L standard deviation of the change in sweat chloride for successful modulator trials (Boyle et al., 2014; Vermeulen et al., 2017), an anticipated 6% of responders would be expected by chance alone. Therefore, the treatment response prevalence will be compared to a reference rate of 6%. For longitudinal FEV1 through day 28 and for secondary endpoints (absolute change in sweat chloride, QOL questionnaire, and weight/BMI from baseline through day 28), means at each time point and changes over time will be summarized along with corresponding confidence intervals estimated by mixed effects models to account for within-subject correlation.

Changes in FEV1 following treatment with Trikafta™ will be correlated with secondary clinical outcome measures. A non-linear Spearman's correlation coefficient will be estimated for each measure paired with iPS cell responses *in vitro*, with corresponding fitted curves displayed graphically along with coordinates for participant's paired *in vivo* and *in vitro* responses.

For other outcomes of interest including sweat chloride levels, quality of life, and weight/BMI, we will also apply a mixed effect model to examine the change in these measures over the study duration. Models will include a subject-specific intercept, to account for variability among subjects prior to the start of the treatment, and a categorical variable for time (baseline, day 14, day 28, day 56). A Dunnett's post-hoc comparisons procedure will be used to determine which time points demonstrated a significant change from baseline. Using the same mixed effects models, we will include  $\Delta$  Isc as predictors of *in vivo* improvement. We will also test the interaction between time and  $\Delta$  Isc to determine when *in vitro* response is most associated with change in clinical response. Adverse events and other safety endpoints will be tabulated and reported using counts and percentages or means and standard deviations, as appropriate.

Because clinical parameters may vary among patients prior to the start of therapy, we will also approach the analysis using a modified N of 1 design configured for the purpose of comparing iPS studies in contrast to the aggregate analysis described above. Using the framework of single

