**Sample size**

We will test the null hypothesis that the true Trikafta™ response rate of NCFBE individuals is  $\leq 1\%$  vs. the alternative hypothesis that the true Trikafta™ response rate is  $\geq 15\%$ . We will initially enroll 16 subjects. If none of these subjects exhibit a clinical response (defined as  $> 5\%$  improvement of % predicted FEV1 from baseline), the study may be considered for termination. Otherwise, we intend to enroll a total sample size of 29 individuals (or 30 subjects, in the unlikely event that an individual discontinues participation; i.e., subjects who do not complete the study will be replaced). In this design, if Trikafta™ is ineffective, the probability of early termination after 16 subjects is 85% and only a 2.8% chance of concluding the drug is effective (type I error). If Trikafta™ is effective, there is a 90.04% chance of reaching this conclusion. If fewer than 2 patients (of 29 patients total) of the overall cohort show a clinical effect, Trikafta™ will be considered ineffective. To demonstrate the ability of iPS cells to predict clinical benefit, 16 (29) patients will provide at least 80% power to detect a significant Spearman correlation of at least  $r = 0.8$  (.53) between the changes in clinical outcomes with changes in short circuit current as measured in iPS cells. Tabular details of this analysis are provided below. Power calculations were performed using PASS v. 14 (Kaysville, UT) with a two-sided Z-test and a significance level of 0.05.

|                            | Cumulative # of responses | Decision                                                                                                             | 95% Confidence Interval (CI) |
|----------------------------|---------------------------|----------------------------------------------------------------------------------------------------------------------|------------------------------|
| Stage 1: Enter 16 subjects | 0                         | Consider Termination of the trial because the agent is ineffective.
Response rate is <math>\leq 1\%</math> | LB of 95% CI is $< 1\%$      |
|                            | At least 1                | Inconclusive result, continue                                                                                        | 95% CI contains 1%           |

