**Protocol Title: Evaluating Trikafta for the treatment of patients with non-cystic fibrosis bronchiectasis (NCFBE)**

|                                                                                                                                                                                                                                   |                                   |                                                                                      |                                       |
|-----------------------------------------------------------------------------------------------------------------------------------------------------------------------------------------------------------------------------------|-----------------------------------|--------------------------------------------------------------------------------------|---------------------------------------|
|                                                                                                                                                                                                                                   |                                   | trial (proceed to stage 2).                                                          |                                       |
| Stage 2: Enter 14 additional subjects                                                                                                                                                                                      | 1 or less
(stage I + stage II) | Consider that the agent is ineffective. Response rate is $\leq 1\%$                  | LB of 95% CI is less than 1%          |
|                                                                                                                                                                                                                                   | 2 or more
(stage I + stage II) | Drug may be effective
Response rate is greater than 1% and not different from 15% | 95% CI contains 15% and LB is $> 1\%$ |
|                                                                                                                                                                                                                                   | 6 or more
(stage I + stage II) | Drug is effective
Response rate is at least 15%                                   | 95% CI LB $\geq 15\%$                 |

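### The stated 2.8% type I error and 90.04% power belong to 2 or more responders of 29, which the decision table says only may be effective; the table's outright effective label (6 or more) is reached about 26% of the time at a true 15% rate

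*Protocol*

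**What the plan says.** Section 7 of the protocol reads the FEV1 responder count in three places.

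- **Opening text of section 7:** "if at least 15% of subjects meet the definition of responder, we will view this as initial evidence of a favorable result". An exact 95% interval by Blaker's method is to accompany the response rate.
- **Sample size text:** the hypotheses are a true rate of at most 1% against at least 15%. "We will initially enroll 16 subjects", with termination considered if none responds; otherwise enrolment continues to 29 (30 to allow for a dropout). The cut-off is "If fewer than 2 patients (of 29 patients total) of the overall cohort show a clinical effect, Trikafta™ will be considered ineffective". The text then gives a 2.8% chance of concluding effectiveness when the drug does not work, and adds "If Trikafta™ is effective, there is a 90.04% chance of reaching this conclusion".
- **Decision table after the Sample size text:** 1 or fewer responders points to an ineffective agent. Two or more is labelled "Drug may be effective", meaning a rate above 1% and not different from 15%. Six or more is labelled effective without qualification, with a rate of at least 15% and a 95% lower bound of at least 15%.

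The table adds 14 subjects in stage 2, so it totals 30 where the text says 29.

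**The concern.** The Sample size text attaches its error rates to a conclusion of effectiveness. The table uses that unqualified word only from 6 responders upward and gives 2 to 5 a weaker label. A reader who takes 90.04% as the chance of the table's top conclusion, or of the favourable result in the opening text, is misled about what 29 subjects can show. No power is stated for either of those bars, and no sentence connects the 15% bar to the table. At stake is the wording of the main efficacy conclusion in an open-label, single-arm trial.

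**Working it through.** **Inputs** (Sample size text and table): null rate 0.01; alternative 0.15; stage 1 of 16 subjects, stopping at 0 responders; total 29, so 13 in stage 2 (or 14 if the total is 30).

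**Formula.** With X1 ~ Bin(16, p) and X2 ~ Bin(n − 16, p),

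P(total ≥ r) = Σ over x = 1 to 16 of P(X1 = x) · P(X2 ≥ r − x).

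For r = 2 this reduces to 1 − P(X1 = 0) − P(X1 = 1) · P(X2 = 0).

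**Step 1: reproduce the protocol's figures with r = 2, n = 29.**

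- Early termination under the null: 0.99^16 = 0.8515 (stated 85%).
- Type I error: 1 − 0.8515 − (16 × 0.01 × 0.99^15) × 0.99^13 = 1 − 0.8515 − 0.1376 × 0.8775 = 0.0278 (stated 2.8%).
- Power: 1 − 0.85^16 − (16 × 0.15 × 0.85^15) × 0.85^13 = 1 − 0.0743 − 0.2097 × 0.1209 = 0.9004 (stated 90.04%).

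All three match. A single-stage rule of 2 or more of 29 would give 94.5% and 3.4%, so the stated figures come from the two-stage rule.

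**Step 2: convert the 15% bar to a count.** 0.15 × 29 = 4.35 and 0.15 × 30 = 4.5, so 5 responders are needed either way (4/29 = 13.8%, 5/29 = 17.2%).

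**Step 3: probability of each bar at a true rate of 15%.**

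| Bar | Where stated | n = 29 | n = 30 |
|---|---|---|---|
| 2 or more | Sample size text; table, middle label | 90.04% | 90.4% |
| 5 or more | 15% sentence in the opening text | 44.2% | 47.2% |
| 6 or more | table, top label | 26.1% | 28.9% |

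By subtraction at n = 29, the chance of 2 to 4 responders is 90.04 − 44.20 = 45.8%.

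**Step 4: check the table's interval statements (exact 95% lower bounds).**

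| Responders | Clopper-Pearson | Blaker |
|---|---|---|
| 2/29 | 0.85% | 1.25% |
| 6/29 | 8.0% | 9.4% |
| 8/29 | 12.7% | 13.6% |
| 9/29 | 15.3% | 16.4% |

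The 2-or-more row (lower bound above 1%) holds with Blaker's method, which section 7 names, but not with Clopper-Pearson. The 6-or-more row fails under both. A lower bound of at least 15% needs 9 of 29, and at a true 15% rate the chance of 9 or more is 2.2%.

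**The case against.** The strongest reply is that these are not three rival rules. The cut-off of 2 in the Sample size text and the table's 2-or-more row are the same rule, and 6 or more is a higher tier of the same table. Within the Sample size paragraph, the conclusion can be read simply as passing the cut-off defined there, and for that the 2.8% and 90.04% are correct. This stands: the figures are not miscalculated, and the table can be read as a graded scale.

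A reader might go further and infer that 2 to 4 responders produce a flat contradiction, with a 45.8% chance of occurring. The documents do not support that. The 15% sentence says what counts as favourable; it does not say that a lower rate is unfavourable. The table already has a label for that range, so 45.8% is the chance of an intermediate result.

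A reader might also infer that the sponsor could choose its rule after seeing the count. The response rate and its exact interval are to be reported whatever the count, and section 20 describes a preliminary data set not intended for FDA submission. Nothing in the documents shows such an intention.

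Nor is 44.2% a sign of a failed design. A bar placed on the observed rate at the alternative itself will be passed only about half the time.

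What the reply does not remove is the mismatch of labels. The Sample size text gives its power to a conclusion of effectiveness, the table gives that unqualified conclusion to a different count, and the 15% bar is left unconnected to both.

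**Conclusion.** The point holds as a mismatch between a correctly computed power and the conclusion it is attached to. The 2.8% and 90.04% apply only to 2 or more responders of 29 under the two-stage rule, and that result supports only a response rate above 1%. The table's unqualified claim has a 26.1% chance at a true 15% rate (28.9% with 30 subjects), and the favourable bar in the opening text 44.2% (47.2%). The 6-or-more row also fails on its own terms, since its lower bound is about 8% to 9% and not 15%.

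These figures assume independent responses, a true rate of exactly 15%, and a stop whenever stage 1 has no responder. The protocol says only that termination may be considered; without that stop, the 2-or-more rule has the single-stage values in Step 1.

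**What to change.** - Name 2 or more responders of 29, under the two-stage design, as the single decision rule. State that 2.8% and 90.04% apply to it alone and that it supports only a response rate above 1%.
- Replace the unqualified word for effectiveness in the Sample size text with wording that matches this.
- Label the 15% sentence in the opening text of section 7 as descriptive, or state its power: about 44% for 5 or more of 29.
- Correct or delete the 6-or-more row. If a lower bound of at least 15% is wanted, the count is 9 of 29. Say that the table's intervals use Blaker's method, because the 2-or-more row depends on it.
- State whether the denominator is 29 or 30.

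The cost is wording and a few figures; sample size and interim look stay as they are. The downside is that the stated power for any claim of effectiveness or a favourable result becomes less attractive than 90%.
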